### Statistical considerations

#### Sample size

As this is an exploratory study, the sample size was based on a feasibility assessment and ensuring that a sufficient number of participants will be recruited to analyse a range of nasal mucosal fluid and salivary time points. It is assumed that fewer samples will be collected than requested, and previous studies have indicated that approximately 75% of participants are likely to provide a sufficient number of samples.^10^ As such, we are vaccinating up to 40 children, expecting 30 participants will meet the minimum required number of samples for primary analysis (measuring viral load). A subset will also provide sufficient nasal cell samples for phenotyping and single-cell analysis as per other similar studies of respiratory pathogens.^11^ We will analyse all available data from study participants who were given the Fluenz vaccine.

#### Per-protocol population

For all objectives, analysis will only be carried out on those participants who receive the LAIV appropriately and who are part of the per-protocol population. For the primary outcome (LAIV viral load over time), the per-protocol population is defined as producing a nasal fluid sample at two or more time points prior to D9 post vaccination. For secondary outcomes, the per-protocol population is defined as having provided two blood samples, two home samples prior to D9 and at least the second nasal cell sample.

Exploratory end points will be analysed in the following populations: participants who have provided at least one nasal cell and blood sample and at least one post-vaccination nasorption sample. For some of the analyses, such as gene expression, a subset of participants will be selected for analysis based on clinical outcomes and availability of samples for the desired time points.

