### Aims and objectives

This exploratory study aims to characterise the immune responses in the nasal mucosa and blood of children receiving the nasally administered LAIV (an infection-like stimulus). This manuscript is written in accordance with protocol version 2.0, dated 29 November 2024. Primary, secondary and exploratory objectives and outcome measures and time points are summarised in table 1.

**Table 1 T1:** Objectives and outcome measures (see online supplemental material 1 for full details)

Objectives	Outcome measures
Primary objective	
Longitudinal assessment of LAIV strain-specific viral loads following vaccination with LAIV	Viral load of LAIV in nasal and saliva samples determined by qPCR
Secondary objectives	
Determine changes in antibody levels to influenza antigens in the mucosa	Antibody levels against influenza strains contained in LAIV determined by ELISA or comparable technical approach
To detect presence of nasal colonisation with pneumococcus or other respiratory pathogens	Detection of pneumococcus, most common respiratory viruses and other respiratory bacteria determined by microfluidic qPCR
To determine changes to influenza-specific antibodies in the systemic circulation	Antibody levels against the influenza strains contained in LAIV by ELISA or comparable technical approaches
To characterise transcriptional changes in mucosal immune cells in response to LAIV vaccination	Transcriptome analysis to identify gene signatures associated with response to vaccination in the nasal mucosa
Exploratory objectives	
To evaluate humoral responses and antigen-specific B cells to LAIV in systemic circulation	Analysis of antigen-specific B cells in systemic circulation using flow cytometry
To evaluate inflammatory responses to LAIV at the mucosa	Analysis of a range of inflammatory markers using Luminex multiplex panel or comparable technical approaches
To evaluate nasal cell populations before and after LAIV	Analysis of changes in cell populations in nasal mucosa by flow cytometry and related assays
To determine B cell receptor and T cell receptor full-length sequences in systemic circulation and compare with immune repertoire and expansion and/or contraction of clonotypes identified at single-cell level in the nasal mucosa	Analysis of scRNAseq and/or bulk transcriptome data to determine B cell receptor and T cell receptor sequences in the nasal mucosa

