### Study objectives and measurements

The primary objective is to assess the influenza viral load of saliva and mucosal lining fluid across the sampling points throughout the study period. Secondary objectives include determining changes in antibody levels in the mucosa and systemic circulation, detecting changes in nasal colonisation with pneumococcus and other respiratory bacteria and viruses and characterising transcriptional changes following LAIV vaccination. A full list of the primary, secondary and exploratory objectives is included in Box 1. Samples will be stored for the duration of the study and thereafter, if consent is given, be transferred to the OVC biobank. All samples are processed by the OVC laboratory and stored on liquid nitrogen or in a −80 °C freezer per the laboratory analysis plan.

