### Microbiological measurements

Viral load will be measured from nasal mucosal lining fluid (nasosorption sample) and salivary samples from V1, home samples and V2 through reverse transcription quantitative polymerase chain reaction (RT-qPCR). Detection of pneumococcus, other respiratory bacteria and common respiratory viruses will be assessed by microfluidic qPCR.

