#### Statistical analysis

The analysis of the primary outcome involves the measurement of LAIV viral load over time. The LAIV load at different time points will be analysed in two ways:

The viral load will be summarised using the number, mean, geometric mean, SD, median, minimum and maximum at each time point. Log-transformed value will be analysed using a generalised estimating equation model, in which treatment, time and the interaction between treatment and time as independent factors after taking the correlation of participants into account. An exchangeable covariance structure will be used. The geometric mean ratio between groups together with their 95% CIs at each time point will be derived. If the interaction effect is non-significant, the interaction term will be dropped and the model refit, including only time and treatment fixed effects.The area under the curve (AUC) of LAIV will be calculated by the trapezoidal rule from log10+1 transformed LAIV load results. The AUC will be summarised using the above descriptive statistics, and the log AUC will be analysed using a generalised linear model with a single factor of treatment. The geometric mean ratio between groups, together with their 95% CIs, will be derived.

For secondary and exploratory outcomes, the immune response data are expected to be highly skewed, and the data will be log-transformed prior to analysis. The geometric mean concentration and associated 95% CI will be summarised by computing the anti-log of the mean of the log-transformed data.

Continuous variables such as LAIV viral load and AUC over time will be summarised according to the number of subjects with non-missing data (n), mean, SD, median, minimum and maximum. Categorical variables such as symptoms and serious adverse events (SAEs) will be summarised according to the absolute frequency and percentage of subjects (%) in each category level. The denominator for the percentages is the number of subjects vaccinated with LAIV with data available, unless noted otherwise.

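### The primary outcome covers nasal fluid and saliva, but the primary population is defined by nasal fluid alone, so children with usable saliva are excluded from the salivary analysis

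*Protocol article*

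**What the plan says.** The protocol article places both specimens in the primary outcome in three sections.

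- Aims and objectives, Table 1, gives the primary outcome measure as "Viral load of LAIV in nasal and saliva samples determined by qPCR".
- Study objectives and measurements states: "The primary objective is to assess the influenza viral load of saliva and mucosal lining fluid across the sampling points throughout the study period".
- Microbiological measurements confirms that both are assayed throughout: "Viral load will be measured from nasal mucosal lining fluid (nasosorption sample) and salivary samples from V1, home samples and V2".

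The Sample size section also refers to nasal and salivary time points when it explains the number recruited.

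The Per-protocol population section then sets the rule for the primary outcome: "the per-protocol population is defined as producing a nasal fluid sample at two or more time points prior to D9 post vaccination". Saliva has no condition of its own. The same section makes the restriction binding for all objectives: "analysis will only be carried out on those participants who receive the LAIV appropriately and who are part of the per-protocol population".

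Two other statements bear on the point. The Sample size section says that all available data from children given Fluenz will be analysed. The Statistical analysis section introduces the primary analysis with "The LAIV load at different time points will be analysed in two ways" and names no specimen.

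**The concern.** A population rule should admit a child to an analysis according to whether that child has data for it. Here the data for salivary load are saliva samples, but admission depends on nasal samples. The two are collected separately, with a strip held in the nostril and a swab held against the buccal mucosa, so a child may tolerate one and not the other. The plan expects fewer samples than requested and lets the strip be held only as long as the child tolerates it, so unequal series are foreseeable.

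Two things are at stake. Valid salivary data on a primary outcome would be discarded for a reason unrelated to their quality. And the planned evaluable number would not describe the salivary analysis. In a study of up to 40 children, a few exclusions are noticeable.

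**Working it through.** **The plan's own figure.** Inputs from the Sample size section: up to 40 vaccinated, about 75% expected to give enough samples. 40 × 0.75 = 30, as stated. The arithmetic is right. The section does not say which specimen the 75% refers to. Since the only minimum-sample rule for the primary outcome is in nasal fluid, the 30 can be read only as a nasal-fluid count.

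**The rule applied to one child.** Ten saliva samples are scheduled: eight at home (days 1, 2, 3, 4, 6, 9, 14 and 21) plus one at each of V1 and V2. A child who gives all ten, but has a nasal sample at fewer than two qualifying time points, fails the rule. That child is left out of the primary analysis, including the salivary load.

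**How many children this could affect.** The documents give no saliva completion rate, so this is a range under assumptions. Let 75% (30 of 40) qualify on nasal fluid. Let *s* be the share who would qualify on saliva under a matching rule of two or more samples before D9. The overlap of the two groups is bounded by:

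- fewest qualifying on both = 40 × max(0, 0.75 + *s* − 1)
- most qualifying on both = 40 × min(0.75, *s*)
- if independent = 40 × 0.75 × *s*

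Saliva-qualified children excluded = 40*s* − both. Nasal-qualified children without enough saliva = 30 − both.

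For *s* = 0.75: fewest on both = 40 × 0.50 = 20; most = 40 × 0.75 = 30; independent = 40 × 0.5625 = 22.5. Excluded: 30 − 30 = 0 up to 30 − 20 = 10.

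| Assumed *s* | Saliva-qualified, of 40 | Qualify on both: range (independent) | Saliva-qualified but excluded: range (independent) | Nasal-qualified, too little saliva: range (independent) |
|---|---|---|---|---|
| 50% | 20 | 10–20 (15) | 0–10 (5) | 10–20 (15) |
| 60% | 24 | 14–24 (18) | 0–10 (6) | 6–16 (12) |
| 75% | 30 | 20–30 (22.5) | 0–10 (7.5) | 0–10 (7.5) |
| 90% | 36 | 26–30 (27) | 6–10 (9) | 0–4 (3) |

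The ceiling of 10 is the 40 − 30 children who fail the nasal rule. The loss is zero only if every child with adequate saliva also has adequate nasal fluid. At 90% saliva completion that is impossible, because 36 children cannot fit within 30.

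**The two population statements.** One section limits analysis to children who meet the sampling rule. The other promises analysis of all available data from vaccinated children. A child with saliva but too few nasal samples is out under the first and in under the second.

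**The case against.** **All available data.** The strongest reply is that the Sample size section would keep the saliva-only child. It would if it stood alone. The Per-protocol population section says the opposite, specifically for analysis and for all objectives, and nothing ranks the two statements. The reply exposes a second conflict and leaves the first in place.

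**Exploratory study.** The sample size rests on feasibility and no power or error rate is claimed. That stands, and it limits the consequence to who is counted and how the salivary results can be read.

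**Children without saliva.** It might be said that the rule also counts children with no saliva as evaluable for saliva. This carries little weight: the Statistical analysis section reports the number with non-missing data, so such a child adds nothing to a salivary summary and the gap would be visible.

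**Stronger readings that the text does not support.** The model terms are "treatment, time and the interaction between treatment and time as independent factors after taking the correlation of participants into account", with no specimen factor, and a single AUC is described. A reader might infer that nasal and salivary values are to be pooled, that one may replace the other when missing, or that the analysed quantity is nasal fluid only. The section says none of these. It leaves the specimen unnamed, and running the same model and AUC once per specimen fits the wording. That detail may properly sit in the full protocol or the analysis plan, which are not shown. For the same reason no fold-change in viral load can be attached to this point: it would need both an assumed gap between the specimens and a pooling step that the plan does not state.

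A reader might also conclude that saliva should become a secondary outcome. That would be a preference. Two descriptive curves, one per specimen, are acceptable in an exploratory study.

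**Conclusion.** The point holds as a mismatch between the primary outcome and the population rule. The outcome includes salivary load; the rule admits children on nasal fluid only and is binding. Separate models per specimen would not remove the problem, because the rule would still decide who enters the salivary model.

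Its size is 0 to 10 children with adequate saliva lost out of 40, or 5 to 9 under independence. The number with adequate data on both specimens lies between 10 and 30. These ranges assume that the 75% is a nasal-fluid rate, that saliva would be judged by a matching rule, and that 50% to 90% of children would meet it. The contradiction itself needs none of these assumptions. The effect is on the evaluable number and on interpretation, and no error-rate or power statement is affected.

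**What to change.** 1. In Per-protocol population, define the primary population by specimen: nasal load by nasal fluid samples, salivary load by saliva samples, each with its own minimum number before D9.
2. In Statistical analysis, add one sentence saying that the generalised estimating equation model and the AUC are run separately for each specimen.
3. In Sample size, say which specimen the 75% and the 30 of 40 refer to.
4. Reconcile the all-available-data statement in Sample size with the restriction in Per-protocol population, so that one rule governs each analysis.

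Saliva can remain part of the primary outcome. The cost is wording; no new samples, visits or assays are needed. The small downside is that the evaluable number may differ between nasal fluid and saliva and would have to be reported for each.

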### Sample collection

Nasal cells will be collected using flocked swabs. One sample per nostril will be obtained at D0 and D28. FloQSwabs flocked swabs are designed for nasal and mid-turbinate sampling. The brush-like texture of flocked swabs dislodges and collects cells for sampling and allows for more effective elution of the sample into the collection medium. To conduct the sampling, the swab will be inserted into the nostril with the participant’s head tilted slightly backwards, keeping the swab near the septum floor along the inferior turbinate and rotated several times while in contact with the inferior turbinate. The swab will be carefully withdrawn, and the sample stored in the collection tube as per the manufacturer’s instructions.

Blood sampling will be performed by trained, experienced staff. Up to 10 mL of blood will be collected at each visit (D0 and D28). The prior application of anaesthetic cream will reduce discomfort for the participant. A maximum of two phlebotomy attempts will be performed at each visit (D0 and D28). If phlebotomy is unsuccessful, the visit may be rescheduled for another day, a finger-prick sample may be attempted, or the procedure abandoned.

Nasosorption samples will be obtained using Synthetic Absorbent Matrix (SAM) strips, developed by Hunts Development Ltd (UK), which are similar to blotting paper. SAM strips absorb mucosal lining fluid while causing minimal discomfort to participants. Nasosorption strips will be held inside the nostril for up to 2 min, or until soaked through, or as tolerated by the participant. These will then be removed and placed in a microcentrifuge tube for storage.

Salivary sampling will be obtained using Oracol sample swabs (or similar), which were developed by Malvern Medical Developments (UK). Swabs will be removed from their packaging and held against the buccal mucosa for up to 2 min until soaked through. These will then be removed and placed back into their packaging with the sponge facing the microcentrifuge tube. The tube will be capped, and the stick of the sponge broken at the breakpoint, and the final cap replaced.

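### One joint per-protocol set governs four secondary outcomes that use different specimens: it excludes children for samples an outcome does not use, yet omits the baseline that change objectives need

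*Protocol article*

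**What the plan says.** The section Per-protocol population first restricts the analysis: "For all objectives, analysis will only be carried out on those participants who receive the LAIV appropriately and who are part of the per-protocol population". The primary set depends only on the specimen analysed: "producing a nasal fluid sample at two or more time points prior to D9 post vaccination". For the secondary outcomes there is one joint condition: "having provided two blood samples, two home samples prior to D9 and at least the second nasal cell sample".

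Table 1 (Aims and objectives) lists four secondary objectives:
- mucosal antibody: "Determine changes in antibody levels to influenza antigens in the mucosa"
- colonisation: "To detect presence of nasal colonisation with pneumococcus or other respiratory pathogens" (the section Study objectives and measurements words this one as changes in colonisation)
- influenza-specific antibody in the systemic circulation, also worded as change
- nasal transcriptome: "To characterise transcriptional changes in mucosal immune cells in response to LAIV vaccination"

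Sample collection states that nasal cells are taken only at day 0 and day 28, and allows at most two phlebotomy attempts per visit. It then says: "If phlebotomy is unsuccessful, the visit may be rescheduled for another day, a finger-prick sample may be attempted, or the procedure abandoned".

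The Sample size section expects 30 of up to 40 children to be evaluable for the primary analysis, on a 75% rate. It also says that all available data from children given Fluenz will be analysed. It gives no expected size for the secondary set.

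**The concern.** A per-protocol condition should ask for the specimens that an outcome needs and no others. This one fails in both directions. It is too strict because each secondary outcome is made to depend on specimens it does not use. It is too loose because it does not secure the baseline from which change is measured.

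In a study of at most 40 young children, samples already collected and usable would be set aside because an unrelated sample is missing. Some children who are retained could still contribute nothing to a change objective. The article also makes two incompatible statements about who is analysed, so two analysts could produce different secondary tables from the same data.

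**Working it through.** **1. The plan's own figure.** 40 × 0.75 = 30, and in reverse 30 / 0.75 = 40. The stated 30 reproduces, but it belongs to the primary set only.

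**2. What each outcome needs against what the rule asks for.**

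| Secondary outcome | Specimen needed | Required but not used | Needed but not required |
|---|---|---|---|
| Mucosal antibody, change | Nasal fluid or saliva at day 0 and later | Two bloods, day 28 nasal cells | Day 0 sample; a late sample (the required home samples fall before day 9) |
| Colonisation | Nasal fluid or saliva | Two bloods, day 28 nasal cells | Day 0 sample, where change is reported |
| Plasma antibody, change | Blood at day 0 and day 28 | Two early home samples, day 28 nasal cells | None |
| Nasal transcriptome, change | Nasal cells at day 0 and day 28 | Two bloods, two early home samples | Day 0 nasal cells |

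**3. Three children under the rule as written.**
- Child A has all nasal fluid and saliva and both nasal cell samples, but one blood sample is never obtained. Child A is excluded from all four outcomes, although only plasma antibody lacks data.
- Child B has both bloods but only one home sample before day 9, or no day 28 swab. Child B is excluded from plasma antibody, for which the data are complete.
- Child C has both bloods, two early home samples and day 28 nasal cells, but no day 0 nasal cells or day 0 mucosal sample. Child C is included, but neither transcriptional nor mucosal antibody change can be computed.

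No arithmetic is needed for this part.

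**4. Illustrative size.** The 75% comes from the Sample size section and stands in here for the home-sample condition. The article gives no success rate for blood or nasal cells, so those below are assumptions.

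If failures are independent, n = 40 × 0.75 × (blood success per visit)² × (day 28 swab success):
- 80% and 85%: 40 × 0.75 × 0.80² × 0.85 = 16.3
- 90% and 90%: 40 × 0.75 × 0.90² × 0.90 = 21.9

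The blood condition alone, with day 28 cells always obtained, leaves 30 × 0.80² = 19.2 or 30 × 0.90² = 24.3. That is about 11 or 6 children lost from outcomes that use no blood.

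If failures strongly coincide, the joint set approaches the smallest single rate: 40 × min(0.75, 0.80, 0.85) = 30, with almost no extra loss. Some dependence is likely, because the second blood and the second nasal cell sample come from the same visit.

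For the missing baseline: if day 0 nasal cells failed in 5–20% of children, 30 × 0.05 = 1.5 to 30 × 0.20 = 6 of 30 could meet the rule with no baseline.

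**The case against.** The strongest reply is that other text softens the rule. The Sample size section promises to use all available data from vaccinated children, and the Statistical analysis section bases percentages on vaccinated subjects with data. Those statements show that the exclusion is not settled. They do not cure the rule, because they contradict its explicit restriction.

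Second, the Per-protocol population section says that for analyses such as gene expression a subset will be chosen partly on sample availability at the desired time points. This may select day 0/day 28 pairs in practice. However, it sits in the exploratory paragraph, leaves the secondary definition unchanged and helps at most one of the four outcomes.

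Third, two blood samples normally mean that both home visits took place, and nasal fluid, saliva and nasal cells are scheduled at those visits. Missing baselines should therefore be uncommon. That stands as a limit on size; the rule still does not secure the baseline.

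Fourth, the study is exploratory, and a common complete-sample set suits its interest in the interplay of mucosal and systemic immunity. That justifies such a set for analyses that combine compartments, but not for single-specimen outcomes.

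A reader might also infer three stronger points that the article does not support:
- **Any failed venepuncture excludes a child.** The rule asks for blood samples, and rescheduling or a finger-prick may supply one. Exclusion follows only if no sample is obtained.
- **Younger children are selectively lost.** This is plausible, but nothing in the article documents it.
- **The analysis wrongly ignores pairing.** The text on secondary outcomes says "The geometric mean concentration and associated 95% CI will be summarised". That describes a summary. It neither proposes comparing day 0 and day 28 as independent groups nor rules out a paired analysis, which may be specified in the SAP.

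**Conclusion.** The point holds as a defect in a stated rule. The single secondary set can remove usable data from all four secondary outcomes and does not secure the baseline for change in mucosal antibody or the nasal transcriptome. It also contradicts the Sample size section. These conclusions follow from the wording alone.

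The size is uncertain. About 16–22 of 40 holds only under the assumed success rates and independent failures; with strongly coinciding failures the set could be as large as about 30. The range to carry forward is therefore about 16 to 30, against 30 expected for the primary set. It would be wrong to read 16–22 as a forecast. The 30 is also not the expected size of an outcome-specific mucosal set, which the article gives no means of estimating.

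The matter should be corrected before analysis, but it does not affect the primary outcome.

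**What to change.** Reconcile the Sample size and Per-protocol population sections so that one statement says who is analysed. Then define the secondary set per outcome:
- Plasma antibody: paired day 0 and day 28 blood.
- Mucosal antibody: day 0 plus at least one of day 14, 21 or 28 in the same matrix (nasal fluid or saliva).
- Colonisation: any valid nasal or saliva result, with day 0 plus a later result where change is reported.
- Transcriptional change: paired day 0 and day 28 nasal cells.

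Show n for each outcome in its table. If a complete-sample set is wanted for analyses linking mucosal and systemic responses, keep it for those only.

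As a supporting suggestion, report the paired geometric mean fold rise with its 95% CI next to the geometric mean concentrations, unless the SAP already does so.

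The cost is wording only, with no added visits or samples. The drawback is that n will differ across secondary outcomes, so the tables will not describe exactly the same children.
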